## Abstract

**Background:**

Although the pathogenesis of acute kidney injury (AKI) in patients with acute coronary syndrome (ACS) undergoing invasive treatment is multifactorial, the role of iodinated contrast media (CM) has been well established. The DyeVert system (Osprey Medical) is designed to reduce the CM volume during invasive coronary procedures while maintaining fluoroscopic image quality.

**Objective:**

The aim of the Renal Insufficiency Following Contrast Media Administration Trial IV (REMEDIAL IV) is to test whether the use of the DyeVert system is effective in reducing contrast-associated acute kidney injury (CA-AKI) rate in patients with ACS undergoing urgent invasive procedures.

**Trial Design:**

Patients with ACS treated by urgent invasive approach will be enrolled. Participants will be randomly assigned into one of the following groups: (1) DyeVert group and (2) control group. In participants enrolled in the DyeVert group, CM injection will be handled by the DyeVert system. On the contrary, in the control group, CM injection will be performed by a conventional manual or automatic injection syringe. In all cases, iobitridol (a low-osmolar, nonionic CM) will be administered. Participants will receive intravenous 0.9% sodium chloride as soon as moved to the catheterization laboratory. The primary end points are CM volume administration and CA-AKI rate (ie, an increase in serum creatinine concentration of ≥0.3 mg/dL within 48 hours after CM exposure). A sample size of at least 522 randomized participants (261 in each group) is needed to demonstrate an 8.5% difference in the CA-AKI rate between the groups (that is, from 19% in the control group to 10.5% in the DyeVert group), with a 2-sided 95% confidence interval and 80% power (*P* < .05).

## Introduction

Acute kidney injury (AKI) is a common complication in patients with acute coronary syndrome (ACS), being treated by invasive approach.^1^^,^^2^ This complication has been associated with higher early and late adverse events.^3^ Although the pathogenesis of AKI in patients with ACS is multifactorial,^4^ the role of iodinated contrast media (CM) has been well established.^5^ Volume expansion represents the cornerstone in contrast-associated acute kidney injury (CA-AKI) prevention.^6^ However, all recommended volume expansion regimens have limited applicability in patients with ST-elevation myocardial infarction (STEMI) and high-risk non–ST-elevation myocardial infarction (NSTEMI) transferred to percutaneous coronary intervention (PCI)-capable centers for emergency invasive treatment. Therefore, in this scenario, it is of outmost importance to limit the CM volume in the attempt to prevent CA-AKI. The DyeVert system (Osprey Medical) is a novel device designed to reduce the CM volume during coronary procedures, while maintaining fluoroscopic image quality.^7^

The aim of the Renal Insufficiency Following Contrast Media Administration Trial IV (REMEDIAL IV) is to test whether the use of the DyeVert system is effective in reducing AKI rate in patients with ACS undergoing urgent invasive diagnostic and interventional coronary procedures.

## Methods

### Recruitment, enrollment, and allocation

This multicenter, randomized, investigator-driven, clinical trial will assess the role of the DyeVert device in limiting AKI rate in patients with ACS. All patients with ACS scheduled for urgent/immediate invasive approach will be screened for inclusion/exclusion criteria (Tables 1 and 2). Diagnosis of ACS (both STEMI and high-risk NSTEMI) will be established in accordance with guidelines, including a typical chest pain history, diagnostic electrocardiographic changes, and serial increase in cardiac biomarker concentrations.^8^, ^9^, ^10^ All patients with inclusion/exclusion criteria satisfied and who will agree to sign the informed consent form will be enrolled into the study. The REMEDIAL IV will be conducted at 4 Italian interventional cardiology centers (Supplemental Methods and Supplemental Table S1). Radial access will be recommended. The study is registered with www.ClinicalTrials.gov (NCT04714736). The number of participants screened, treated, and analyzed will be reported according to the CONSORT guidelines.

**Table 1 tbl1:** Inclusion criteria

Condition	Definition
Age ≥18 y	–
Acute coronary syndrome	ST-elevation myocardial infarction^a^ High-risk non–ST-elevation myocardial infarction^b^: a) Refractory angina b) Signs or symptoms of heart failure or new or worsening mitral regurgitation c) Hemodynamic instability d) Recurrent angina or ischemia at rest or with low-level activities despite intensive medical therapy e) Sustained VT or VF f) Recurrent dynamic ST-T wave changes, particularly with intermittent ST-elevation
Urgent or immediate (within 2 h) invasive approach	Coronary procedure with iodinated contrast media administration

VT, ventricular tachycardia; VF, ventricular fibrillation.

a According to the Fourth Universal Definition of Myocardial Infarction.^8^

b According to the current guidelines.^9^^,^^10^

**Table 2 tbl2:** Exclusion criteria

Condition	Definition
Women who are pregnant	–
Recent contrast media exposure	Contrast media exposure within 48 h
End-stage CKD on chronic dialysis	Both hemodialysis and peritoneal dialysis
Multiple myeloma	–
Patients referred from a spoke center for an invasive treatment but not hospitalized in the institutions conducting the study	–
Current enrollment in any other study when enrollment in the REMEDIAL IV would involve deviation from either protocol	–

CKD, chronic kidney disease; REMEDIAL IV, Renal Insufficiency Following Contrast Media Administration Trial IV.

### Protocol

Participants included into the study will be randomly assigned into 2 groups (Central Illustration): (1) DyeVert group and (2) control group.

**Central Illustration fig1:**
[figure not shown]
**Schematic representation of the study design.** STEMI, ST-elevation myocardial infarction; NSTEMI, non–ST-elevation myocardial infarction; LVEDP, left ventricular end-diastolic pressure.

#### The DyeVert group

In participants enrolled in this group, CM injection will be handled by the DyeVert system. The DyeVert system (Osprey Medical) is a device designed to reduce the CM volume during coronary procedures, while maintaining fluoroscopic image quality.^7^ The DyeVert Plus EZ Contrast Reduction Systems is compatible with manual contrast injection, whereas the DyeVert Power XT Contrast Reduction System is compatible with automated contrast injection (ACIST; ACIST Medical Systems). (Supplemental Methods). It allows for the modulation of the CM volume during an injection. During an injection, the DyeVert system diverts a portion of the injected CM through a secondary fluid pathway controlled by a pressure-compensating diversion valve. This allows a decrease in overinjection of CM and less aortic reflux. The diversion valve provides variable resistance in the secondary fluid path to ensure a flow rate to the patient, which results in an adequate image quality. The valve is constructed in a way that the diversion pathway resistance automatically increases with higher injection pressures and decreases with lower injection pressures, proportionally decreasing or increasing CM delivered to patients, respectively. The diverted CM is temporarily stored in the reservoir and is returned to the injection syringe when the physician aspirates CM for the next injection. The associated Contrast Monitoring System (Osprey Medical) displays CM volume injected (in milliliters), split in attempted, delivered, and saved (the last reported as both absolute value and percentage vs the total). The DyeVert system can be used in conjunction with 4F to 6F diagnostic catheters and 5F to 7F guide catheters.

#### The control group

CM injection in this group will be performed by a conventional manual injection syringe or automatic injection device (ACIST Medical Systems).

### Iodinated contrast media

Iobitridol (Xenetix 350; Guerbet; 350 mg iodine/mL), a nonionic, low-osmolality (915 mOsm per kilogram of water) CM, will be used in all participants. Strategies for limiting the CM volume are as follows^11^: (1) in the control group, angiograms will be performed with an injection of CM using a 10-cm^3^ syringe; this provides strict control of CM delivery by limiting the volume of contrast that can be administered in a single injection; (2) catheters with side holes will be strictly avoided during PCI; (3) when exchanging catheters, unused CM is withdrawn from the catheter lumen (eg, by back-bleeding through an opened “Y”-connector or by aspirating residual CM from the catheter using a syringe); (4) “tests” with “puffs” of CM are discouraged; and (5) left ventriculography will not be permitted. The administration of a CM volume of >3× glomerular filtration rate (GFR) is suggestive of increased risk of CA-AKI.^12^ A new CM source bottle will be used in the control group when using manual syringe injection to be sure about the starting CM volume level. After the procedure, the end volume on the CM source bottle will be marked to indicate the CM volume ending point, and the amount of remaining CM within the syringe will be documented. Then, the total volume of CM used from the bottle will be measured using a graduated cylinder.

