CM volume administered is an independent predictor of CA-AKI.^5^^,^^27^ Owing to the nonlinear relationship between CM volume and AKI, some “safe” thresholds have been proposed (Supplemental Table S7). However, others have reported a linear relationship between CM volume and AKI rate.^21^^,^^28^ It has been reported that a 30% reduction in CM volume could translate into a 12.8% reduction in AKI.^21^ SCAI expert consensus statement on best practices in the cardiac catheterization laboratory emphasizes quality indicators related to CM volume reduction and monitoring.^11^ To date, the use of manual injections with a manifold remains the preferred technique in most catheterization laboratories.^29^ Although CM flow rate and maximum injection pressure can be preset in automatic systems, the manual syringe provides constant pressure feedback to the operator that might favor better modulation of the injection. The “a clinical trial for contrast media volume reduction and incidence of CIN” (AVERT) tested the efficacy of the DyeVert system to reduce the CM volume used during coronary angiographic procedures without impairing image quality and to prevent AKI.^30^ The AVERT trial demonstrated that CM volume is significantly lower in patients receiving DyeVert in comparison with control subjects (36.9 ± 10.9 mL vs 62.5 ± 12.7 mL; *P* < .001). This resulted in a 41% decrease in the volume of CM used. The observed reduction in CM volume used was most evident in patients who underwent PCI. The volume of CM spared with the use of AVERT was directly related to the complexity of the PCI procedure, with 31% and 46% reductions in CM volume used when 2 and 3 lesions were treated, respectively.

Other methods for CM volume minimization have been tested. However, biplane angiography has not been proven to significantly reduce CM volume injected.^31^ Moreover, in the minimizing contrast utilization with IVUS guidance in coronary angioplasty trial (MOZART), intravascular ultrasound–guided PCI reduced the CM volume used compared with angiography-guided PCI.^32^ However, intravascular ultrasound is not widely used and can increase procedure costs and duration.

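### The control injection technique, and so the comparator for contrast volume, is described inconsistently, and the text shown does not say whether injection mode is set before allocation

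*Protocol article*

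**What the plan says.** The abstract of the protocol article states that "in the control group, CM injection will be performed by a conventional manual or automatic injection syringe". The Methods subsection on the control group agrees: "CM injection in this group will be performed by a conventional manual injection syringe or automatic injection device (ACIST Medical Systems"). On these two statements a control patient may be injected by either mode.

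The Iodinated contrast media subsection lists five strategies for limiting contrast volume. The first reads "in the control group, angiograms will be performed with an injection of CM using a" 10-cm³ syringe, and the reason given is that "this provides strict control of CM delivery by limiting the volume of contrast that can be administered in a single injection". It carries no condition on mode and names the control group only. The other four strategies name no arm. Further down, the same subsection says "A new CM source bottle will be used in the control group when using manual syringe injection", which treats manual injection as one case among controls.

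The DyeVert group subsection describes one version of the device for manual injection and one for automated injection, so either mode can occur in that arm too. The Statistical analysis section gives 1:1 allocation in permuted blocks of 4, mentions no stratification by mode or centre, and lists manual versus automatic injection among the prespecified subgroups. Contrast volume is a primary end point together with the AKI rate.

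**The concern.** The trial asks how much contrast DyeVert saves against conventional injection, so conventional injection has to mean one thing. A centre that used the automatic injector in a control patient would comply with the control group subsection and breach the first contrast-limiting strategy. Two centres could run different comparators, each following the article.

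The article itself treats mode as possibly relevant to volume. Its Discussion says that "the manual syringe provides constant pressure feedback to the operator that might favor better modulation of the injection", and mode is a prespecified subgroup. If mode were decided once the arm is known, it would be a post-randomisation variable. Two results would then be exposed. The overall volume comparison could include a difference between injectors as well as the effect of DyeVert. The manual-versus-automatic subgroup would condition on something that allocation may have influenced.

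**Working it through.** **No figure to reproduce.** The plan gives no expected volume by mode, no mode share by arm and no expected volume saving for this trial. The 261 patients per group rest on the AKI rates, and this point leaves them unchanged.

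**Step 1: the statements side by side.**

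| Place | What it implies for controls |
|---|---|
| Abstract, Trial Design | either mode |
| Methods, The control group | either mode |
| Iodinated contrast media, strategy (1) | 10-cm³ syringe, no condition |
| Iodinated contrast media, source bottle sentence | manual is one case among controls |
| Statistical analysis, subgroups | both modes occur |

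Strategy (1), taken as written, is at odds with the other four.

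**Step 2: what each reading does to the subgroup.** If strategy (1) covers manual controls only, each mode stratum can hold patients from both arms and the subgroup can be estimated. If it covers all controls, the automatic stratum holds DyeVert patients only, and no within-mode comparison exists there. The wording therefore decides whether a prespecified analysis can be done.

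It also bears on measurement. The bottle and graduated-cylinder procedure is introduced for manual controls, so whether it covers every control depends on the same reading.

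**Step 3: how mode could bias the volume comparison.** Let S be the true DyeVert saving, taken as equal in both modes; d the mean extra volume with automatic rather than manual injection; and a_C and a_D the shares of automatic injection in the control and DyeVert arms. Then

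expected difference (control − DyeVert) = S + d × (a_C − a_D).

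- If a_C = a_D, the second term is zero. This holds in expectation if mode is set before allocation, and also if each centre uses one mode for both arms.
- If d > 0 and a_C > a_D, the result flatters DyeVert.
- If d > 0 and a_C < a_D, the result works against DyeVert. Controls all on the hand syringe (a_C = 0) are the extreme case, with a bias of −d × a_D.

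**Step 4: illustration only.** The documents give neither d nor the shares. Assuming d of 10 to 30 mL and share differences of 10 to 30 points:

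- low end: 10 × 0.10 = 1 mL
- high end: 30 × 0.30 = 9 mL

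The sign is open.

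**Step 5: what is left if mode is set beforehand.** With an assumed 50% automatic share and 261 per arm, the chance imbalance in share has standard error √(2 × 0.5 × 0.5 / 261) = 0.044, or 4.4 points. At d = 10 to 30 mL that is 10 × 0.044 = 0.4 mL to 30 × 0.044 = 1.3 mL. This is ordinary random error, not bias.

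**The case against.** The strongest reply is that the text nearly resolves itself. Two places allow either mode, the subgroup presupposes both, and the bottle sentence supplies the condition that strategy (1) lacks. On this view a qualifier was dropped and one phrase repairs it. That is a fair account of the likely cause. It does not remove the inconsistency: strategy (1) is unconditional as written, is offered as a volume-limiting measure, and concerns the comparator for a primary end point.

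A second reply is that this is a condensed article. The sentence on the device versions is followed by a reference to the Supplemental Methods, which are not shown and may say how mode is assigned. This stands. The silence on timing is therefore a point to confirm, not an established defect, and it is weaker than the contradiction.

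Three stronger readings are tempting and are not supported:

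- A reader might infer that an unblinded operator picks the mode after allocation. No section says who chooses or when, and mode may follow from each laboratory's equipment.
- A reader might infer that a false DyeVert benefit is to be expected. The direction is open. A per-injection cap in controls alone would lower comparator volume and work against DyeVert, and no section says that the DyeVert arm uses a larger syringe. The Discussion remark on manual feedback is hedged and carries no estimate.
- A reader might set the 1 to 9 mL against the saving in the earlier DyeVert trial cited in the Discussion (62.5 − 36.9 = 25.6 mL) and report 4% to 35%. Both inputs are assumed and the denominator belongs to another trial, so that is not an estimate for this one. For AKI the documents give no difference by mode at all.

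Nor is the manual-versus-automatic subgroup useless in itself. It is compromised only if mode is chosen after allocation, or if the unconditional reading leaves no automatic controls.

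**Conclusion.** The contradiction stands on the text alone. Strategy (1) under Iodinated contrast media conflicts with the abstract, with the control group subsection, with its own subsection's later wording and with the prespecified subgroup. The comparator for the co-primary volume end point is inconsistently described.

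The risk of bias is conditional. It needs mode to be chosen after allocation, its share to differ between arms, and mode to affect volume; none of the three is established. If all three held, the volume comparison and the subgroup could be biased in either direction by an amount that the documents do not allow to be computed. The point is worth correcting because the correction is cheap. It does not show that the trial's result would be wrong.

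**What to change.** 1. Reconcile the abstract, the control group subsection and strategy (1) under Iodinated contrast media so that they describe the same control technique. State for each of the five contrast-limiting measures which arm it applies to. Which technique to specify is for the investigators.
2. Record the planned injection mode before randomisation and keep it whichever arm is assigned. Record the mode actually used as well, so that departures are visible.
3. Define the manual-versus-automatic subgroup by planned mode, not by the mode used.
4. If the Supplemental Methods or the full protocol already set the mode before allocation, cite that rule in the article; item 2 is then met.

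Stratifying randomisation by mode or centre is optional. Once mode is set beforehand only chance imbalance remains, and stratifying by both would mean 4 × 2 = 8 strata and a revised list.

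The cost is one extra case report form field before randomisation, in an urgent setting where time is short. Sample size and equipment do not change.

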### Volume expansion regimen

Normal saline (0.9% sodium chloride) will be used in all instances. The volume expansion rate will be 3 mL/kg/h and will start as soon as the patient will arrive into the catheterization laboratory. Volume expansion will continue during the procedure and for at least 6 hours postprocedure. However, in case of hemodynamic instability (Supplemental Methods and Supplemental Table S2), volume expansion will be performed at the rate of ≤1.5 mL/Kg/h or, if deemed clinically contraindicated, will not be started at all. Intraprocedural volume expansion will be guided by left ventricular end-diastolic pressure (LVEDP), according to the Prevention of Contrast Renal Injury with Different Hydration Strategies (POSEIDON) trial^13^ (Supplemental Table S3). LVEDP measurement will be made in all patients by placing a 5F or 6F pigtail catheter in the midcavity of the left ventricle at the beginning of the procedure and before CM injection. LVEDP will be measured at the beginning of the isometric ventricular contraction at the “Z” point. A total volume expansion of >960 mL is considered the optimal cutoff volume to prevent CA-AKI.^2^

### Biomarkers of renal function and injury

Serum creatinine (sCr), cystatin C, blood urea nitrogen, sodium, and potassium concentrations will be measured at the baseline (ie, as soon as the participant will arrive in the emergency room or in the catheterization laboratory room before CM injection) and every day during the hospital stay until discharge; additional measurements will be performed in all cases of deterioration of baseline renal function. Estimated GFR will be calculated by applying the Chronic Kidney Disease Epidemiology Collaboration (CKD-EPI) equation.^14^ Chronic kidney disease is defined as a GFR of <60 mL/min/1.73 m^2^. The risk scores for predicting CA-AKI will be estimated according to the Mehran score^15^ and Gurm score^16^ (Supplemental Methods and Supplemental Tables S4 and S5).

### Study end points

The primary end point of the trial are CM volume and the rate of AKI, defined as an increase in a sCr concentration of ≥0.3 mg/dL within 48 hours after CM administration or the need for dialysis.^17^ Secondary end points will include the following: (1) an increase in the sCr concentration of ≥0.5 and/or ≥25% mg/dL within 72 hours after CM exposure; (2) the severity of AKI assessed according to the KDIGO criteria^17^: stage 1/risk, a sCr concentration increase of ≥0.3 mg/dL or ≥1.5-1.9 times from the baseline level; stage 2/injury, a sCr concentration increase of ≥2.0-2.9 times from the baseline; and stage 3/failure, a sCr concentration increase of ≥3.0 times from the baseline or the need for dialysis; (3) changes in the serum cystatin C concentration at 24 and 48 hours after CM exposure; (4) the rate of acute renal failure requiring dialysis (defined as a decrease in renal function necessitating acute hemodialysis, ultrafiltration, or peritoneal dialysis within the first 5 days postintervention); (5) the length of in-hospital stay, calculated as the sum of the number of days since admission until discharge from the hospital; (6) the rate of in-hospital and 1-month, 6-month, and 12-month major adverse events, such as death, major bleeding, renal failure requiring dialysis, and sustained kidney injury. Major bleeding will be defined according to the BARC criteria.^18^ Sustained kidney injury is defined as a persistent ≥25% GFR reduction, compared with baseline and the last available value during the follow-up.^19^

